## Abstract

**Background:**

Postmastectomy pain syndrome (PMPS) is a prevalent chronic pain condition that occurs after breast cancer surgery, often impairing quality of life in survivors of breast cancer. Despite its prevalence, no standardized treatment has been established. Acupuncture has been reported to be an efficacious intervention for the management of chronic pain and may be an effective treatment for PMPS.

**Objective:**

This study aims to explore the effectiveness and safety of integrative treatment of acupuncture-based intervention for PMPS.

**Methods:**

This is a single-center, single-arm, prospective interventional study. Eligible participants are patients with breast cancer who experience chronic postoperative pain in the chest, neck, or shoulder with a numerical rating scale (NRS) score ≥4, are at least 6 months postcurative treatment, have no evidence of disease recurrence, and are not receiving anticancer treatment at enrollment. Participants will receive the intervention once weekly for 12 sessions, followed by a 4-week observation period. The primary end point is the change in the average pain NRS score from baseline to week 16.

**Results:**

The study commenced in October 2023 and is scheduled to continue through March 31, 2027. The first participant was enrolled on October 24, 2023. As of the manuscript submission, 24 patients have been enrolled.

**Conclusions:**

This study will explore the potential role of an integrative treatment of acupuncture-based intervention in the management of PMPS. The results will contribute to the evidence base for acupuncture in PMPS and inform the design of future clinical studies.

## Introduction

Breast cancer is the most common cancer among women and is treated with a multidisciplinary approach, including surgery, radiotherapy, anticancer drugs, and hormonal therapy [1]. The prognosis for early-stage breast cancer is generally favorable, with a 5-year survival rate of more than 85% [2]. Although long-term survival has improved, many survivors experience persistent treatment-related complications, including pain, upper limb dysfunction, lymphedema, and chemotherapy-induced peripheral neuropathy [3-7]. Among these, chronic pain is prevalent and persistent [8-10].

Postmastectomy pain syndrome (PMPS) is a chronic pain condition that develops after breast cancer surgery and is characterized by stabbing, aching, or burning sensations in the chest, neck, or shoulder [11]. It has been reported to affect 20% to 50% of patients following surgery [12-15] and to impair quality of life in survivors of breast cancer [16]. Various treatments for PMPS have been reported, including surgical interventions (such as fat grafting and peripheral nerve surgery), cutaneous laser therapy, nerve blocks, adjuvant analgesics for neuropathic pain, and physical therapy [17-23]. Although the potential benefits of nonpharmacological treatments have been reported, the available evidence remains limited, and no standardized treatment has been established [24].

Acupuncture has been shown to be beneficial for the management of chronic noncancer pain and cancer-related pain [25-28]. The Society for Integrative Oncology and American Society of Clinical Oncology guideline states that acupuncture may be offered for general cancer pain and musculoskeletal pain [29]. The Survivorship Care Guidelines of the American Society of Clinical Oncology Breast Cancer include acupuncture as a recommended treatment option for chronic pain [30]. However, the specific efficacy of acupuncture for PMPS has not been differentiated. Evaluating the effectiveness of integrative treatment of acupuncture-based intervention, as practiced in Japanese clinical settings, may contribute to establishing a novel nonpharmacological treatment option and addressing an unmet clinical need in breast cancer survivorship care.

## Methods

### Study Objective

The objective of this study is to explore the effectiveness and safety of integrative treatment of acupuncture-based intervention for PMPS.

### Study Design and Setting

This is a single-center, single-arm, prospective interventional study. This study will be conducted according to the protocol based on the Standards for Reporting Interventions in Clinical Trials of Acupuncture guideline [31].

### Ethical Considerations

This study protocol was approved by the Institutional Review Board of the National Cancer Center Hospital (research subject number 2023‐091). Written informed consent will be obtained from all participants prior to enrollment. Participants will not receive any financial compensation for participation in this study.

### Eligibility Criteria

The inclusion criteria are as follows: pathologically diagnosed stage I to III breast cancer; ≥6 months since curative surgery with no evidence of recurrence; undergoing observation without anticancer treatment (endocrine and anti–human epidermal growth factor receptor 2 therapies are permitted); pain in the chest, neck, or shoulder on the surgical side that developed after surgery; a pain numerical rating scale (NRS) score ≥4 during the past 24 hours; age ≥18 years; an Eastern Cooperative Oncology Group Performance Status (ECOG PS) of 0 or 1; a neutrophil count ≥1000/μL and a platelet count ≥50,000/μL within 28 days before enrollment; and no change in pain medication within 7 days prior to enrollment.

The exclusion criteria are as follows: upper limb lymphedema on the surgical side; bilateral pain in the chest, neck, or shoulder; painful comorbidities (such as fibromyalgia and arthritis); severe psychiatric disorders; severe chronic comorbidities (such as cardiovascular, hepatic, renal, gastrointestinal, and hematologic diseases); pregnancy or breastfeeding; and a history of previous acupuncture for PMPS.

### Recruitment and Consent

Participants will be recruited from the outpatient setting of the Department of Palliative Care. Patients diagnosed with PMPS and referred to the Department of Palliative Care for pain management will be screened for eligibility. The palliative care physician will provide a detailed explanation of the study and obtain written informed consent. Participation in the study will be entirely voluntary, and patients will be informed that refusal to participate will not affect their clinical care.

### Concomitant Medications

Participants will be required to maintain stable doses of medications that may influence pain throughout the study period. These include opioids (morphine, oxycodone, hydromorphone, fentanyl, tapentadol, tramadol, and methadone), antidepressants, anticonvulsants, benzodiazepines, acetaminophen, nonsteroidal anti-inflammatory drugs, and corticosteroids.

Initiation of new analgesic medications during the study period will not be permitted. Any unavoidable changes in medication will be documented. However, as-needed benzodiazepine use for sleep will be permitted.

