### Sample Size and Statistical Analysis

In this study, we considered that a difference of approximately 2 points in pain scores before and after the intervention, corresponding to the minimal clinically important difference for pain advocated by the Initiative on Methods, Measurement, and Pain Assessment in Clinical Trials, would be clinically meaningful. Therefore, we assumed a mean difference of 2 points in pain scores from baseline to week 16, a SD of 4 points, and a correlation coefficient of 0.5 between preintervention and postintervention values. As a result, the required sample size was calculated to be 27 at a 1-sided significance level of 5% and 80% power. The sample size was set at 30 cases to allow for dropouts during the trial.

The analysis population will include patients who have received at least one dose of the intervention. All data collected during the observation period after discontinuation of the intervention will be included in the analysis. In principle, missing data will not be imputed in this study, and the analysis will be conducted using only the observed values (observed case analysis). However, if missingness is largely attributable to worsening clinical condition, the results of the observed case analysis may be biased toward overestimation. Therefore, sensitivity analyses using appropriate imputation methods will be conducted to assess the robustness of the findings (prepared before data are fixed).

As an analysis of the primary end point, a paired *t* test (1-sided test) will be conducted on the null hypothesis that “the mean difference between the average pain NRS before intervention and at 16 weeks is greater than or equal to zero.” The significance level for this hypothesis is set at 5% for 1-sided testing, and the corresponding 2-sided 90% CI will be calculated for the mean change from baseline to week 16. If the hypothesis testing is significant, it will suggest the effectiveness of the intervention in this exploratory study and support the planning of a confirmatory trial.

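### Week-16 pain scores recorded after a new or increased pain-relevant medication count as benefit of the combined intervention, and no planned analysis examines them

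*Protocol article*

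**What the plan says.** Three parts of the protocol article bear on this point.

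- **Concomitant Medications.** The rule is strict: "Participants will be required to maintain stable doses of medications that may influence pain throughout the study period". It goes on: "Initiation of new analgesic medications during the study period will not be permitted". It then accepts that the rule will sometimes be broken: "Any unavoidable changes in medication will be documented". As-needed benzodiazepine for sleep is the one stated exception. The section gives no consequence for the analysis, and a medication change is not among the reasons for stopping protocol treatment under Discontinuation Criteria and Safety Monitoring.
- **Sample Size and Statistical Analysis.** The population is set: "The analysis population will include patients who have received at least one dose of the intervention". Data after stopping are kept: "All data collected during the observation period after discontinuation of the intervention will be included in the analysis". In principle nothing is imputed, and "the analysis will be conducted using only the observed values (observed case analysis") is the rule. The exception concerns missingness caused by clinical worsening, for which "sensitivity analyses using appropriate imputation methods will be conducted to assess the robustness of the findings". A significant one-sided paired t test is to be read as suggesting effectiveness and as support for a confirmatory trial.
- **Study Design and Setting.** "This is a single-center, single-arm, prospective interventional study". There is no comparator.

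**The concern.** A week-16 NRS recorded after a new or increased analgesic is an observed value. It is not missing, so the planned sensitivity analyses do not reach it. Under the rules as written it goes unchanged into the paired t test. It also goes into the 1-, 2- and >2-point and the 30% and 50% reduction rates, the personal pain goal rate and the time to a 2-point reduction.

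The direction of the error matters. A start or increase is most plausible in a patient who is not improving. If the drug then lowers the pain, a failure of the intervention is recorded as a success. With a single arm there is no reference group in which the same co-medication could be seen. Participants have been referred for pain management with an NRS of at least 4, and they are followed for 4 weeks after the last session, so such changes are credible even under the prohibition.

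The Limitations section concedes that placebo effects and natural recovery cannot be separated from the effect of treatment. It does not mention co-medication, which differs from those two in that it is recorded patient by patient and can be examined without a control group.

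**Working it through.** **1. The plan's own figure.** Inputs from Sample Size and Statistical Analysis: mean difference 2, SD 4, correlation 0.5, one-sided 5%, power 80%.

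- SD of the change = √(4² + 4² − 2 × 0.5 × 4 × 4) = √16 = 4.
- Paired t test, noncentral t: power is 79.8% at n = 26 and 81.2% at n = 27. The stated 27 is reproduced, and 27 / 0.9 = 30 matches a dropout allowance of about 10%.

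The sample size is not in dispute. The question is which values enter the test.

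**2. The mean fall needed for significance.** With n = 27 and SD of change 4:

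- t(0.95, 26 df) × 4 / √27 = 1.706 × 0.770 = 1.31 points.

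**3. Path of one value through the rules.** Take a patient who has had at least one session, has a documented analgesic increase before week 16 and reports an NRS at week 16.

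- Population rule: included.
- Data after stopping the sessions: included if the patient stopped.
- Observed-case rule: value used as reported.
- Sensitivity analyses: not applicable, because the value is present.

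No stated step treats this value differently from any other.

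**4. Size, under assumptions.** The documents give neither the number of such patients (k) nor the drug-related fall (r), so both are assumed. The inflation of the mean fall is k × r / 27. The last column is the approximate rejection rate of the nominal 5% test if the intervention has no effect. It uses a noncentral t with mean shift f × r and variance 16 + f(1 − f)r², where f = k / 27.

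| k of 27 | r (points) | Inflation of mean fall | Share of 1.31 | Approx. rejection rate |
|---|---|---|---|---|
| 3 | 1 | 3 × 1 / 27 = 0.11 | 8% | 6.6% |
| 3 | 3 | 3 × 3 / 27 = 0.33 | 25% | 10.9% |
| 5 | 1 | 5 × 1 / 27 = 0.19 | 14% | 7.9% |
| 5 | 3 | 5 × 3 / 27 = 0.56 | 42% | 16.6% |

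A wider assumed range, 5% to 30% of patients and 1 to 3 points, gives an inflation of 0.05 to 0.90 points and a rejection rate of 5.7% to 28.5%. Dose reductions would act in the opposite direction and are not in these figures.

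**The case against.** The strongest reply has four parts.

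- **The article is condensed.** No sentence says how scores after a medication change are handled, and supplementary analyses by medication use are often left to an analysis plan. Such a plan may contain a rule. This stands as a caution. But the article does more than stay silent: it fixes the population, the use of data after stopping, the observed-case rule and the purpose of the sensitivity analyses. Together these settle what happens to the value.
- **New analgesics are forbidden.** This stands. The point concerns departures from the rule that the protocol itself expects, and there may be few. A reader might infer that the plan counts rescue medication as benefit. It defines no rescue medication, so that wording is not supported.
- **Using all observed data is a recognised treatment-policy choice, and causal claims are already disclaimed.** Both stand. A reader might infer that including data after stopping is itself an error, or that the effect is credited to acupuncture. Neither follows: the inclusion avoids dropping patients who stop, and Limitations says that results reflect the combined package. Yet a significant test is still read as suggesting effectiveness, and that reading is what co-medication can distort.
- **The size is speculative.** This stands. A reader might compare the inflation with a smaller threshold, such as 0.66 points at an SD of change of 2. That SD is not the plan's; its inputs give 4. It would also be too much to say that every randomised trial balances such changes, since they can differ between arms.

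**Conclusion.** The point holds in a limited form. Followed as written, the protocol counts a week-16 NRS lowered by a new or increased pain-relevant medication as benefit of the combined intervention, and nothing planned would show how far the result depends on such scores.

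With 3 to 5 of 27 patients and a drug-related fall of 1 to 3 points, the mean fall is inflated by about 0.11 to 0.56 points. At the plan's SD of change of 4 this is 8% to 42% of the 1.31 points needed for significance. Inflation of this size is not enough alone to bring the mean fall to that threshold, but it raises the chance of a false signal and can tip a borderline result.

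Both the frequency and the drug effect are assumptions, and the true inflation may be close to nil. A reader might infer that the primary result will be false or that the primary analysis should be replaced; the documents support neither. What is justified is a fixed rule for these scores and a report of how many there are.

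**What to change.** Keep the all-data primary analysis. Before data lock, add the following to the analysis plan:

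1. Flag each patient with a documented start or increase, before the week-16 assessment, of a medication listed under Concomitant Medications. Exclude the permitted as-needed benzodiazepine for sleep. Report the number flagged beside the primary result.
2. Count flagged patients as non-responders for the week-16 point-reduction, percentage-reduction and pain-goal end points.
3. For time to a 2-point reduction, do not credit a reduction first reached after the change.
4. Add one prespecified supplementary analysis of the primary end point that gives no credit for improvement after the change. One option sets the week-16 NRS of flagged patients to the worse of the baseline and observed values, so that a score above baseline is kept. A multiple-imputation equivalent would avoid the understated variance that fixed substitution can bring.

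The cost is one derived flag from information already to be documented, plus a little analysis. The downside is a conservative second estimate, which may discard genuine improvement, for example where it preceded the change or the drug was taken for an unrelated complaint. No clinical medication rule changes. With 24 of the planned 30 patients enrolled at manuscript submission and the sensitivity analyses to be prepared before the data are fixed, the rule can still be set in advance.

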### Intervention

The intervention will be administered by licensed acupuncturists with at least 5 years of clinical experience. All acupuncturists will complete a standardized training program for the study intervention (3 days, 8 hours/day; total 24 hours) prior to study initiation.

The intervention consists of acupuncture, moxibustion, hot pack therapy, and self-care instructions. Acupuncture is the primary treatment, while moxibustion, hot packs, and self-care instructions are considered supplementary.

Acupuncture is performed in the Japanese style and includes static needling, motion needling, and teishin (noninsertive acupuncture). Disposable stainless steel needles (0.16‐0.20 mm in diameter and 40‐50 mm in length; SEIRIN) are used for static and motion needling. For static needling, needles are inserted to a depth of approximately 5 mm and retained for 5 to 10 minutes. For motion needling, needles are inserted to a depth of 5 to 20 mm. After needle insertion, slow passive movements are performed 2 to 3 times, including wrist flexion or extension; forearm pronation or supination; upper arm rotation; scapular protraction or retraction; and shoulder flexion, extension, and abduction. Elicitation of a muscle twitch response is not required.

Teishin is performed using nonpenetrating metallic instruments (approximately 1.0‐12.0 mm in diameter and 110 mm in length), applying gentle compressive stimulation with light rubbing for 1‐ to 2 minutes.

Acupuncture points are listed in Tables1  2. Essential points (Figure 1) are applied to all participants, and additional points are selected according to individual symptoms and findings on physical examination. If shoulder range of motion is restricted, additional needles will be applied to the affected muscles.

**Table 1. T1:** Essential acupuncture points.

		Essential points
Unilateral		
	Static needling	BL25, CV4, CV12, LI18, SI16, and Ex-B7
	Static needling and teishin	LU1, LU2, ST13, and KI27
	Static needling and motion needling	LI14, LI15, SI9, SI10, SI11, SI12, SI14, TE14, BL12, and BL17
Bilateral		
	Static needling	BL10, BL13, BL18, BL20, BL23, GB12, GB20, GB21, KI7, KI10, LR4, LR8, and ST25

**Table 2. T2:** Additional acupuncture points.

		Additional points
Unilateral		
	Static needling and motion needling	LU6, LI10, PC4, and TE9
	Static needling, motion needling, and teishin	Pectoralis major muscle, supraspinatus muscle, infraspinatus muscle, subscapularis muscle, rhomboid muscle, deltoid muscle, biceps brachii muscle, triceps brachii muscle, trapezius muscle, latissimus dorsi muscle, teres major muscle, teres minor muscle, and levator scapulae muscle
Bilateral		
	Static needling	ST36, BL56, BL57, and BL60

**Figure 1. F1:**
[figure not shown]
Essential acupuncture points (for right-sided postmastectomy pain syndrome).

Moxibustion and hot pack therapy are applied to areas of the chest wall, axilla, and upper limbs presenting abnormal sensations. After each treatment session, participants receive self-care instructions, including self-massage of the anterior chest wall, axilla, and upper limb, as well as stretching exercises to improve shoulder range of motion.

### Study Schedule

The study schedule is presented in Table 3. The intervention will commence within 28 days of enrollment and will be administered once weekly for 12 sessions. A 4-week follow-up period will be conducted after completion of the intervention phase (Figure 2).

**Table 3. T3:** Study schedule.

	Enrollment	Weeks 1‐12	Weeks 4, 8, and 12	Week 12	Week 16
Informed consent	✓				
Laboratory data	✓			✓	
Eligibility screening	✓				
Personal pain goal	✓				
ECOG PS^a^	✓		✓		✓
Intervention		✓			
Pain NRS^b^	✓	✓			✓
Shoulder joint range of motion	✓		✓		✓
Shoulder36	✓		✓		✓
EORTC QLQ-C30^c^	✓		✓		✓
Five viscera score	✓		✓		✓
ESAS^d^	✓				✓
HADS^e^	✓				✓
Adverse event			✓		✓

a ECOG PS: Eastern Cooperative Oncology Group Performance Status.

b NRS: numerical rating scale.

c EORTC QLQ-C30: European Organisation for Research and Treatment of Cancer Quality of Life Questionnaire Core 30.

d ESAS: Edmonton Symptom Assessment System.

e HADS: Hospital Anxiety and Depression Scale.

**Figure 2. F2:**
[figure not shown]
Trial procedure flow. NRS: numerical rating scale; PMPS: postmastectomy pain syndrome.

At enrollment, baseline data will be collected, including age, sex, surgical side, treatment history, pain location, and personal pain goal. Blood tests will be performed within 28 days prior to enrollment and at week 12.

Clinical assessments, including ECOG PS and shoulder joint range of motion, will be performed at enrollment and every 4 weeks thereafter. Adverse events will be evaluated every 4 weeks from intervention initiation. Patient-reported outcomes will be collected at predefined time points, as specified in Table 3.

### Discontinuation Criteria and Safety Monitoring

The protocol treatment will be discontinued if any of the following conditions are met: participant request for discontinuation, recurrence of breast cancer, development of serious comorbidities, or adverse events deemed by the physician to preclude continuation of the study intervention.

Safety monitoring will be conducted through assessments by acupuncturists at each intervention session, physician assessments every 4 weeks, and additional physician assessments at the participant’s request. If adverse events are identified by acupuncturists during each session, they will be reported to a palliative care physician, who will provide appropriate evaluation and management.

### Data Collection Methods

Patient-reported outcomes, including pain NRS, Shoulder36, EORTC QLQ-C30, five viscera score, ESAS, and HADS, will be completed by participants using self-administered questionnaires. Clinical assessments, including ECOG PS, shoulder joint range of motion, and adverse events, will be conducted by physicians during scheduled study visits. All study data will be entered into a secure electronic data capture system by trained study personnel.

